## Methods

### Design

The overall design of StAND is a four-year quasi-experimental, natural experiment, with two conditions (INT and CNT), four measurement occasions, and individual-level measurement of exposures and outcomes (see Fig. 1 for a conceptual diagram for the study). Four INT parks were selected by Detroit Audubon and five comparable CNT parks were selected, based on size, existing trees/plants, and proximity to other bird habitats. All adults (i.e. aged ≥18 years) living in a CNT or INT park neighborhood (defined in the following text) were invited to participate. Baseline (t = 0) and three annual measurements (t = 1 to t = 3) post-restoration will be conducted on participating individuals with the intention of having a longitudinal panel study design. However, we considered sampling alternatives depending on attrition, as others studies have done [42]. If attrition is higher than expected (> 25% at t = 1), then additional participants will be recruited at each time point, yielding a repeated cross-sectional design, with a nested panel. If assessments at certain time points are missing within the panel for some participants, we will assume that data from our unbalanced panel is missing at random.

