### Sample size

Assuming a longitudinal panel design, sample size assessments for the study are based on achieving 82% power to test the hypotheses. The effect measure is a difference-in-differences (DID) — in hypotheses 1–3, i.e., the expected change in PA from baseline to three-years post-restoration in INT parks compared to the corresponding change in CNT parks. Hypotheses 3–6 concern a DID in stress outcomes. A review of the literature on PA [46] and cortisol [47] suggests an effect size (EF) of 0.35 could be posited. Accordingly, we calculate our sample size requirements to detect an EF of 0.35 or better with 82% power. Two other design features are: a serial correlation *r* between repeated measures over time and intra-class correlation (ICC) *ρ* for clustering within neighborhood parks. In community-intervention studies such as ours, *ρ* is small [48–51]. Plausible values from the literature and our own experiences, suggest *r* ≥ 0.35 and *ρ ≤* 0.004. With a total of nine parks (4 INT, 5 CNT), we will need a sample of 450 participants, or 50 per park, to detect EF = 0.35 with 82% power, based on a two-sided test at significance level 5%. Because attrition is expected over the study period, we will recruit a total of 620 participants at t = 0 (baseline) to account for attrition of 15% at t = 1 and another 10% at t = 2 and 5% at t = 3. Our sample size assessment may also be deemed conservative as it does not account for potential influence of fixed covariates, which should increase precision on the intervention effect estimate by reducing residual variance resulting in a positive effect on power.

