To address missingness in our response data, we will employ strategies for imputation [139]. The techniques described above allow missing at random (MAR). Inverse probability weighting [140] will be investigated to accommodate missing data patterns that are not MAR. To minimize bias in analysis, we will adjust for factors that may be unbalanced between groups and examine the robustness of our conclusions under deviations of model assumptions. Below, we outline specific analyses for each hypothesis to be tested.

#### Hypothesis 1

We will separately evaluate average activity counts/minute and average moderate-to-vigorous minutes over the one-week observation period for each of the data collection periods. The predictor of interest is binary: INT versus CNT.

#### Hypothesis 2

The primary outcome, ‘green PA’, will be average activity counts/minute and average moderate-to-vigorous minutes over the one-week observation period while in parks and greenspaces in Detroit, as a subset of all activity.

#### Hypothesis 3

We hypothesize there will be an association between PA and the visual and auditory exposures. Instead of a binary predictor of interest, we will use continuous predictors for visual and auditory park exposures. Interaction terms between positive and negative exposures will also be assessed, as evidence suggests that negative sounds deplete the restorative benefits of natural sounds, [141] and that parks are often dominated by noise [45, 142].

#### Hypothesis 4

Each stress outcome will be evaluated separately and treated continuously. We will also explore potential mediators (e.g., PA) by adding each to mixed models as fixed terms, and adjusted mediation and partial correlation coefficients explored. We will adjust for prescription medication history and symptoms of acute illness as potential confounders.

#### Hypothesis 5

We will assess relationships with each stress indicator, in turn.

#### Hypothesis 6

We hypothesize there will be an association between each stress indicator and these exposures.

#### Hypothesis 7

We will compare INT and CNT groups from baseline through three-years post-restoration for changes in CRP and A1C (continuously measured) between INT and CNT groups. We will also consider the inclusion of prescription medication history and symptoms of acute illness as potential confounders.

#### Hypothesis 8

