We will compare INT and CNT groups from baseline through three-years post-restoration for changes in blood pressure, hip-to-waist ratio and BMI (continuously measured) between INT and CNT groups.

Despite our best effort to recruit and retain a longitudinal panel of participants, we may face problems with attrition higher than the projected attrition rates of 15% at t = 1, another 10% at t = 2, and 5% at t = 3. With these levels, our longitudinal panel becomes unbalanced but valid inference can be made under the assumption that attrition is at random (MAR). We describe another strategy, *repeated cross-sections*.

By repeated cross-sections we mean a series of independent samples are drawn at the subsequent times t = 1, 2, 3 following the initial baseline sample at t = 0. It could happen that a participant in the baseline sample is also in any of the subsequent samples, but this is at random. With repeated cross-sectional samples, we cannot estimate *within participant* change in outcomes, which is the key advantage of the longitudinal panel approach. However, we can still assess patterns of change at an aggregate level as explained in the following text.

Consider an outcome $$ {\mathit{\mathsf{Y}}}_{\mathit{\mathsf{it}}} $$ at time *t* in the *i-*th participant, and the linear model $$ {{\textsf{Y}}}_{{\textsf{i}\textsf{t}}}={\mathbf{\textsf{x}}}_{{\textsf{i}\textsf{t}}}^{\prime}\beta +{\alpha}_{{\textsf{i}}}+{\varepsilon}_{{\textsf{i}\textsf{t}}} $$ with exogenous covariates $$ {\mathbf{\textsf{x}}}_{{\textsf{it}}} $$, *t* = 0, 1, 2, 3. We aggregate each sample into *C* cohorts defined as participants who share common characteristics such as age, sex, neighborhood park, etc. Aggregation of participants to the cohort level *c* replaces the model by the cohort model $$ {\overline{{\textsf{Y}}}}_{{\textsf{c}\textsf{t}}}={\overline{{\mathbf{\textsf{x}}}^{\prime}}}_{{\textsf{c}\textsf{t}}}\beta +{\overline{\alpha}}_{{\textsf{c}}}+{\overline{\varepsilon}}_{{\textsf{c}\textsf{t}}} $$, *c* = 1, …,*C*, *t* = 0, 1, 2, 3. (Bar notation refers to averages over participants within cohort/time). Our observed data become a pseudo-panel of repeated observations on cohorts over time, and estimation of differences between INT and CNT cohorts could be compared over time, although the cohorts are not comprised of the same participants from one time point to the other. Some technical issues will need to be addressed to ensure a consistent estimator of *β* [143–146].

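### Inverse probability weighting is named for missing data that are not MAR, but no selection model or sensitivity parameter is given that would make it valid there

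*Protocol article*

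**What the plan says.** All of the following is in the protocol article.

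- **Design**, on participants with missing assessments: "we will assume that data from our unbalanced panel is missing at random".
- **Statistical analysis**, on missing responses: "To address missingness in our response data, we will employ strategies for imputation [139"]. The next sentence reads "The techniques described above allow missing at random (MAR"). Then comes the sentence at issue: "Inverse probability weighting [140] will be investigated to accommodate missing data patterns that are not MAR". It names no model for how response depends on the unobserved outcome, and no sensitivity parameter.
- **Statistical analysis**, directly after that: a commitment to "examine the robustness of our conclusions under deviations of model assumptions". It mentions neither missing data nor MNAR.
- **Statistical analysis**, on attrition at the projected rates: "valid inference can be made under the assumption that attrition is at random (MAR").
- **Sample size**: "we will recruit a total of 620 participants at t = 0 (baseline"), a figure set "to account for attrition of 15% at t = 1 and another 10% at t = 2 and 5% at t = 3".

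**The concern.** The mixed model and the imputation are presented as MAR methods, and weighting is presented as the step beyond them. Ordinary weighting does not take that step. Each retained person is weighted by the inverse of an estimated probability of being observed, and that probability is fitted to recorded data. Two people with the same record get the same weight, even if one was far more likely to stay because of a year-3 activity level that nobody sees for those who left. Weighting can move an analysis from MCAR to MAR, or widen the set of variables given which MAR is assumed. It cannot remove dependence on the missing value itself.

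What is at stake is the claim the trial can make about robustness. If the mixed-model and weighted estimates agree, the sentence as written would let that agreement be reported as evidence against harm from informative dropout, which it does not test. The exposure is not small: over a quarter of the baseline sample is expected to be lost before the time point to which Hypothesis 1 refers.

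**Working it through.** **1. Planned loss.** Inputs from Sample size: 620 recruited, attrition of 15%, 10% and 5%, target 450.

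- Retained fraction, applied in sequence: 0.85 × 0.90 × 0.95 = 0.72675.
- 450 / 0.72675 = 619.2, which reproduces the plan's 620.
- 620 × 0.72675 = 450.6 retained.
- Lost by t = 3: 1 − 0.72675 = 27.3%.

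This counts attrition only. The rule requiring at least 4 days of valid wear can add missing primary-outcome data.

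**2. Bias if MAR fails.** Let δ be the amount, in outcome SDs, by which dropouts' unseen year-3 mean lies below its MAR prediction, and m the fraction lost. An estimator that is correct under MAR is then biased upward in each arm by m × δ, so

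DID bias = m_INT × δ_INT − m_CNT × δ_CNT.

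The article gives one attrition schedule for both arms. With m = 0.273 in each, bias = 0.273 × (δ_INT − δ_CNT). The δ values below are assumptions; the documents give none.

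| δ_INT − δ_CNT | DID bias (SD) | Share of 0.35, same SD unit |
|---|---|---|
| 0 | 0 | 0% |
| 0.25 | 0.273 × 0.25 = 0.068 | 20% |
| 0.5 | 0.273 × 0.5 = 0.137 | 39% |

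Sample size does not say which SD the 0.35 refers to. If it is the SD of change, and r = 0.35, then 0.35 × √(2(1 − 0.35)) = 0.35 × 1.140 = 0.399 outcome SD. The shares become 0.068/0.399 = 17% and 0.137/0.399 = 34%.

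**3. Does weighting remove it?** Simulation with 2,000,000 subjects, outcome SD 1, r = 0.35 between baseline and t = 3, 27.3% missing in each arm, true DID 0.35. Weights came from a logistic model on arm, baseline and their interaction. The dropout mechanisms are assumed.

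| Dropout mechanism | Completers | MAR imputation | Weighting |
|---|---|---|---|
| MAR: depends on baseline, opposite direction by arm | 0.444 | 0.352 | 0.352 |
| MNAR, same in both arms, OR 1.65 per SD | 0.352 | 0.352 | 0.352 |
| MNAR in INT only, OR 1.28 | 0.421 | 0.412 | 0.412 |
| MNAR in INT only, OR 1.65 | 0.484 | 0.468 | 0.468 |
| MNAR in INT only, OR 2.0 | 0.526 | 0.506 | 0.506 |
| MNAR in INT only, OR 2.7 | 0.584 | 0.558 | 0.558 |

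Under MAR, weighting does its job. Under arm-specific MNAR it leaves a bias of 0.412 − 0.35 = 0.06 to 0.558 − 0.35 = 0.21 SD and matches MAR imputation to three decimals. By step 2 those biases correspond to arm differences in δ of 0.062/0.273 = 0.23 to 0.208/0.273 = 0.76.

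**4. Effect on the test.** With no true effect, the INT-only mechanisms gave biases of 0.058, 0.114, 0.154 and 0.206. For a change-score DID with 200 INT and 250 CNT participants and ICC 0.004, SE = √(1.3 × (1 + 49 × 0.004) × (1/250 + 1/200)) = 0.118. Two-sided 5% type I error under a normal test becomes about 8%, 16%, 26% and 41%.

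**The case against.** Several points against the concern are fair.

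- **A reader might infer that the plan has no check against informative dropout.** The article does not support that. It makes a general promise to examine robustness when model assumptions fail, and a statistical analysis plan that is not shown may say more. What stands is narrower: the article names no method that is valid under MNAR.
- **A reader might infer that the mixed model, imputation and weighting all rest on one identical assumption.** They need not. MAR is relative to the variables conditioned on. The study records length of residence, employment, income and perceived safety, and, under Risk of bias assessment, perceived gentrification and local home prices. Weights built on these could make MAR hold where it fails for the minimal GROUP and TIME model. This is a real use of weighting, but still a MAR analysis.
- **Weighting can be extended to MNAR** through a selection model with a fixed sensitivity parameter, and the cited reference cannot be seen here. But the article states no such parameter, and without one the sentence does not describe that method.
- **A reader might link gentrification to differential dropout.** The article names gentrification as a possible consequence of the intervention and plans to measure it. It says nothing of move-outs or unequal attrition, so that link is conjecture.
- **The sizes are illustrative.** They need departures from MAR that differ by arm; the same mechanism in both arms left the DID essentially unbiased.
- **The article sets no rule** that agreement between mixed model and weighting would count as robustness. The risk lies in how the sentence would be used.

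The article's condensed form does not answer the main point. The sentence makes a positive statement about what the method does, so the fault is not missing detail.

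**Conclusion.** The concern holds in a limited form. The article gives weighting a task that, as described, it cannot perform, and names nothing else that is valid when dropout depends on the unseen outcome. The two statements that assume MAR, in Design and in the attrition text, are openly stated assumptions and are not themselves errors.

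The planned 27% loss follows from the article's own figures. The consequence for the DID ranges from nothing, if departures from MAR and loss fractions are equal in the two arms, to 0.07 to 0.14 SD if the departures differ by 0.25 to 0.5 SD. That upper part is about 20% to 39% of the planned effect in a common SD unit. These are not predictions: the δ values and odds ratios are assumed, the direction could be reversed, and nothing shows that dropout will be informative. The primary model stands. What does not stand is the stated safeguard for the case in which MAR fails, and it should be corrected before outcomes are analysed.

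**What to change.** 1. Reword the sentence so that weighting is an alternative analysis under MAR. Put auxiliary variables that the mixed model omits into the weight model, such as length of residence and perceived gentrification. For people who leave, use values recorded before dropout.
2. Name one analysis for not-MAR dropout, for the primary outcome's DID at t = 3, that carries an explicit sensitivity parameter. Delta-adjusted (pattern-mixture) multiple imputation is one suitable choice, with δ varied separately in INT and CNT and including equal values. Weighting under a selection model with a fixed parameter for the unseen outcome is another. Report the tipping point, that is, the combinations of δ at which the conclusion changes.
3. Fix the range of δ, and the SD unit in which δ and the 0.35 are expressed, before outcomes are analysed.

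The cost is a wording change and a modest amount of programming, with no new data.

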## Background

Individuals living in socioeconomically deprived inner cities have disproportionately high rates of obesity, Type 2 diabetes, cancer and cardio-metabolic conditions, all of which have stress- and physical inactivity-related etiologies [1–14]. The cost of these diseases is enormous, where the direct annual medical costs for obesity exceed $300b [15], and societal tolls include declining or stagnating life expectancy, particularly in low-income communities [16]. Low-income neighborhoods experience dual risks, whereby physical activity (PA) levels are low and stress levels are high [17, 18]. Stress and physical inactivity can both lead to downstream inflammatory changes that alter body composition and metabolic and immune functions linked to chronic disease [19–22]. Studies underscore the twinned benefits of weight management and lowered stress that engaging in PA confers [23]. Lower stress, regardless of PA, assists with sustained weight loss [24] and improved cardio-metabolic health [25], making it an attractive goal for health benefits.

To induce change in PA and stress on a population level, researchers and city planners are exploring features of the built environment, such as greenspace (e.g., parks), that may promote healthy lifestyles [26, 27]. Parks serve as places to engage in PA in direct contact with nature — called ‘green PA’ — which has been shown to lower anxiety [28] and perceived stress [29, 30] over and above the effects of indoor PA [23] or outdoor PA without greenery [31]. In addition, cross-sectional research indicates that passive exposure to greenspace (e.g., visual, as in the sight of plants and trees, and auditory, as in birdsong) may lower stress [32, 33]. However, not all residents living near parks visit the parks or engage in PA, and, empirically, the relationship between neighborhood greenspace and PA is inconsistent (for a review [34]). Even so, greener neighborhoods consistently predict lower obesity rates across age groups and rural/urban settings [35–41]. One possible explanation for these findings is that healthier people simply choose to live in greener areas. Yet another possible explanation is that the greenness-obesity relationship is influenced not only by PA but by stress reduction.

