### Objectives

The aims of StAND are to observe the effects of ecological restoration of parks on PA, stress and cardio-metabolic health outcomes from baseline through three-years post restoration using a quasi-experimental design. The hypotheses are:

#### Hypothesis 1

Compared to participants in control (CNT) park neighborhoods, participants in intervention (INT) park neighborhoods will have increased PA levels at three-years post-restoration.

#### Hypothesis 2

Compared to participants in CNT park neighborhoods, participants in INT park neighborhoods will have increased levels of ‘green PA’ at three-years post-restoration.

#### Hypothesis 3

Across both INT and CNT parks, the quality of visual and auditory exposures (positive and negative) will affect PA levels.

#### Hypothesis 4

Compared to participants in CNT park neighborhoods, participants in INT park neighborhoods will have lower stress levels as indexed by measures of cortisol, perceived stress, and anxiety at three-years post-restoration.

#### Hypothesis 5

Participants with higher levels of PA and ‘green PA’ will have lower stress.

#### Hypothesis 6

The quality of visual and auditory exposures (positive and negative) will affect stress levels.

#### Hypothesis 7

Compared to participants in CNT park neighborhoods, participants in INT park neighborhoods will have improved glycated hemoglobin A1C (A1C) and C-reactive protein (CRP) at three-years post-restoration.

#### Hypothesis 8

Compared to participants in CNT park neighborhoods, participants in INT park neighborhoods will have lower blood pressure, body mass index (BMI), and hip-to-waist ratios at three-years post-restoration.

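### The 82% power and the difference-in-differences effect measure are claimed for hypotheses 3, 5 and 6, which are not INT-versus-CNT contrasts; for hypotheses 3 and 6 the pooled exposure slope supports an association, not an effect

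*Protocol article*

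**What the plan says.** **Sizing (Protocol article, Sample size).** The section opens by saying that "sample size assessments for the study are based on achieving 82% power to test the hypotheses". It continues: "The effect measure is a difference-in-differences (DID) — in hypotheses 1–3", explained as the change in physical activity (PA) from baseline to year 3 in INT parks against the corresponding change in CNT parks. It then adds: "Hypotheses 3–6 concern a DID in stress outcomes". Hypothesis 3 therefore sits in both families. The inputs are an effect size of 0.35, two-sided 5%, serial correlation r of at least 0.35, intra-class correlation ρ of at most 0.004, and 50 participants in each of nine parks (4 INT, 5 CNT).

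**Hypotheses (Objectives).** Hypotheses 1, 2 and 4 compare INT with CNT neighborhoods. Hypothesis 3 is framed across both kinds of park and says that exposure quality affects PA. Hypothesis 5 says that participants with more PA and green PA have lower stress. Hypothesis 6 reads: "The quality of visual and auditory exposures (positive and negative) will affect stress levels".

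**Tests (Statistical analysis).** For hypothesis 3: "Instead of a binary predictor of interest, we will use continuous predictors for visual and auditory park exposures". Hypothesis 6 is tested as an association of each stress indicator with the same exposures. Hypothesis 5 is given one line on relationships with each stress indicator. The general model is a GLMM with random effects, containing GROUP, TIME and GROUP×TIME as a minimum, with exposure listed among participant characteristics.

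**The concern.** There are two linked problems.

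1. A power figure derived for a two-group contrast of changes is attached to tests with no two-group contrast. A reader would credit hypotheses 3, 5 and 6 with 82% power that the Sample size section does not calculate for them, and could read a null result there as informative.

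2. For hypotheses 3 and 6 the Objectives state an effect. In a random-effects model, a single coefficient for an exposure that varies over time is a weighted mix of two associations: between residents (whose usual exposure is higher) and within residents (what happens when exposure changes). The between-resident part is open to the kind of rival explanation that the Background raises for earlier greenness–obesity findings: "One possible explanation for these findings is that healthier people simply choose to live in greener areas". Rejecting the null for the mixed slope does not by itself support a claim that exposure affects PA or stress.

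**Working it through.** **Step 1: reproduce the 82%.** Inputs from Sample size: 4 × 50 = 200 INT and 5 × 50 = 250 CNT participants; effect 0.35; r = 0.35; ρ = 0.004; two-sided 5%. In both variants SE = √[V × (1/200 + 1/250)] = √(V × 0.009), and power = Φ(0.35/SE − 1.96).

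- (a) Design effect applied to the change score: V = 2(1 − 0.35) × [1 + 49 × 0.004] = 1.3 × 1.196 = 1.555. SE = 0.1183, power = Φ(0.999) = 84.1% (84.0% with a t reference on 448 df).
- (b) Park-by-time component uncorrelated over years: V = 1.3 + 2 × 49 × 0.004 = 1.692. SE = 0.1234, power = Φ(0.876) = 81.0%.

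The stated 82% lies between the two. The recruitment figure also agrees: 620 × 0.85 × 0.90 × 0.95 = 450.6. Every term belongs to a binary INT/CNT comparison.

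**Step 2: set sizing against test.**

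| Hypothesis | Sample size | Objectives / Statistical analysis |
|---|---|---|
| 1, 2 | DID in PA | INT vs CNT |
| 3 | DID in PA and DID in stress | PA on continuous exposures, across both arms |
| 4 | DID in stress | INT vs CNT |
| 5 | DID in stress | stress on PA and green PA |
| 6 | DID in stress | stress on exposures |

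If the second range is a slip for 4–6, hypothesis 3 still stands in the first family, and 5 and 6 still do not fit the second.

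**Step 3: power for a slope.** The document gives no exposure variance, no within-resident share of it and no expected slope, so these are assumptions. Take 450 residents × 4 waves, outcome SD 1, r = 0.35, and a between-resident share of exposure variance (ICCx) of 0.3, 0.5 or 0.8. The within-resident SE is √{0.65 / [450 × 3 × (1 − ICCx)]}. The slope detectable with 82% power is (1.960 + 0.915) × SE.

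| ICCx | SE | Detectable slope (outcome SD per exposure SD) | Power, slope 0.05 | Power, slope 0.10 |
|---|---|---|---|---|
| 0.3 | 0.0262 | 0.075 | 48% | 97% |
| 0.5 | 0.0310 | 0.089 | 36% | 90% |
| 0.8 | 0.0491 | 0.141 | 17% | 53% |

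Reading 0.35 as a slope does not return 82% either: power is then essentially 100% in all three rows.

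**Step 4: what the pooled slope contains.** Within-resident information is 1350(1 − ICCx)/0.65. Between-resident information is 450[ICCx + (1 − ICCx)/4]/(0.35 + 0.65/4). The between-resident share of the weight is 22%, 35% and 64% for ICCx 0.3, 0.5 and 0.8.

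A simulation (1,000 runs per cell) set the true within-resident effect to zero. The model had GROUP, TIME, GROUP×TIME, exposure and a participant random intercept, with no covariates and no park effect. Let c be the assumed correlation between a resident's usual exposure and usual outcome level. Rejection at two-sided 5%:

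| c | ICCx 0.3 | 0.5 | 0.8 |
|---|---|---|---|
| 0 | 5.5% | 4.8% | 4.6% |
| 0.1 | 11% | 16% | 28% |
| 0.2 | 26% | 45% | 78% |

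A within-resident estimator stayed at 4–6% throughout. Adding the resident's mean exposure to the model, checked at c = 0.3, gave 5–6%. A separate simulation with time indicators only and 1,500 runs per cell gave similar pooled rates: 15% and 44% at ICCx 0.5, and 27% and 75% at ICCx 0.8, for c = 0.1 and 0.2.

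**The case against.** The strongest reply has five parts.

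- **The sizing error is only wording.** The 450 and the 82% reproduce for the study's main contrast, and hypotheses 1, 2 and 4 are untouched. This is true and limits the severity, but the published statement still gives three tests a property they do not have.
- **The planned test is of association.** A reader might infer that self-selection makes the tests of hypotheses 3 and 6 invalid, with the rates in Step 4 as their type I error. The document does not support that. The Statistical analysis section hypothesizes an association, and a between-resident association is one. The rates are errors only against the causal wording in the Objectives.
- **The rates are assumed.** Neither c nor ICCx appears in the document, and at c = 0 there is no inflation. The simulations omit nature-relatedness and perceived safety, which the Survey section lists as possible confounders. All residents live within 0.5 km of a study park drawn from one pool of barely maintained spaces, so choosing a home for park quality is less plausible than in general. This stands. Adjustment for measured factors, however, cannot remove unmeasured stable differences.
- **A within-person term is not clean either.** One exposure weight is the resident's own GPS time in view of the park, so a more active week can raise it. The 4–6% holds because the simulation has no time-varying confounding or reverse causation. This stands.
- **Parameterization can be left to an analysis plan.** This is fair: the article does not rule out a mean/deviation split. The point is therefore what an effect claim would need, not that the split is missing. A later plan could add it but would not correct the power statement.

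**Conclusion.** The sizing point holds on the text alone. The 82% is reproduced (81–84%) only for the binary INT-versus-CNT DID, so it applies at most to hypotheses 1, 2 and 4. Three of the eight hypotheses (3, 5 and 6) have no power calculation, and under the assumptions in Step 3 within-resident slope power could be anywhere from about 17% to 97%.

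The modeling point holds in a limited form, for hypotheses 3 and 6 only. An undivided slope cannot by itself carry the claim that exposure affects PA or stress. How misleading it might be depends on an unknown correlation between usual exposure and usual outcome level, and the problem vanishes if that correlation is zero.

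A reader might extend this to hypothesis 5. The Objectives do not support that: hypothesis 5 compares participants with higher and lower PA and makes no effect claim, so testing it on within-person change would replace the stated hypothesis.

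**What to change.** **Sample size.** Limit the DID effect measure and the 82% to hypotheses 1 and 2 (PA) and 4 (stress). Remove the double listing of hypothesis 3. State that no power was calculated for hypotheses 3, 5 and 6.

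**Statistical analysis, hypotheses 3 and 6.** Among panel members, enter each time-varying exposure as two terms: the participant's mean over time and the deviation from that mean. Base any conclusion that exposure affects the outcome on the deviation coefficient. If the split is not made, report the pooled slope as an association only.

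**Hypothesis 5.** Leave it as a between-participant association.

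**Cost.** Wording and one extra derived term per exposure, with no new data. The power claim becomes narrower, and the within-person interval is wider than the pooled one: the detectable slopes are 0.075, 0.089 and 0.141, against 0.066, 0.072 and 0.084 pooled, for ICCx 0.3, 0.5 and 0.8. The split removes stable confounding only, not time-varying confounding or reverse causation. It is unavailable for participants seen once under the repeated cross-section fallback.
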